### Data sources

In order to measure all outcomes, indicators, and covariates, each study assessment will collect detailed data from study participants. We will use audio computer-assisted self-interview (ACASI) to limit social desirability biases in reporting sensitive behaviors (for example, sexual behaviors) [68]. Interviewers will be trained in the use of the ACASI program and survey to assist respondents as needed. To protect against the risk of loss of confidentiality during and after the trial, all data will be maintained on a password-protected local server. Study datasets will be de-identified prior to analysis.

We will collect the following information:

Demographic characteristics of participants (at baseline), which will include age, sex, race and ethnicity, years of formal education, income, employment status, health insurance, living arrangement including homelessness, number of children (under 18), and history with the criminal justice system (that is, arrests and incarcerations). This information will be used to describe the study sample, to assess for any differences between intervention groups, and to test for selective attrition.

Sexual behaviors: We will collect data on the total number of sex partners in the past 3 months, total number of vaginal sex partners and anal sex partners, total number of unprotected vaginal and total number of anal sex partners, and total acts of unprotected vaginal/anal sex.

Drug use: We will ask about the frequency, duration, and amount of substance use, including alcohol, cannabis, methamphetamine, cocaine, heroin, club-drugs, and mis-used prescription drugs. We will assess injection drug use, including the types of drugs injected and the sharing of needles and other drug paraphernalia (for example, spoons and cotton balls). We will also ask about overdoses and treatment for overdose (that is, the use of naloxone). At baseline, we will measure these behaviors over the 3 months before the interview. These measures will be repeated at 1- and 3-month follow-ups, with adjustments to the recall period.

Utilization of drug treatment services: We will ask the following three questions at baseline and at both follow-up visits: (1) Are you in treatment right now? (2) What treatment are you undergoing? (for example, detox) and (3) How many days have you been in this treatment?

Linkage to medical care: We will also collect data on initiation of treatment among HIV and/or HCV positive patients, using the following questions: (1) Did you have an appointment with a medical provider for HIV services? (2) Did you have an appointment with a medical provider for HCV services? (3) Number of medical appointments made and appointments attended since the last interview, as well as initiation of ART and HCV treatment?

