### Study intervention

Patients randomized to the intervention group will thus receive an offer to participate in on-site bundled rapid HIV/HCV testing. Those who accept this offer will receive pre-test information about testing procedures and education, be tested and receive results during the same visit as testing, and be provided post-test counseling and support services according to the protocol developed through our ADAPT-IT^3^ process. Patients with reactive HIV and/or HCV antibody test results will be actively linked immediately to a healthcare provider for further evaluation and confirmatory testing (see Fig. 1). Patients randomized to the control group will receive the standard of care (SOC). The SOC is venipuncture whole blood laboratory-based HIV and HCV testing with delayed results (enzyme immunoassay). Patients may not receive pre-test information, results, and post-test counseling, especially if non-reactive or negative test result(s). Linkage to care in the SOC is accomplished by referral to a healthcare provider within the participating SUD treatment organization or by passive referral to other health facilities. After the end of the follow-up period (see below), all patients in the control group will be offered access to the on-site bundled rapid HIV/HCV testing intervention. This will include all procedures (that is, rapid HIV/HCV testing, post-test counseling, and linkages to care), as appropriate. Trained study staff will obtain written informed consent from all patients prior to enrollment. Additionally, trained supervisors will monitor the safety and efficacy of the trial intervention on a regular basis. They will ensure that all study procedures are conducted and that data are generated, documented, and reported in compliance with the protocol and applicable regulations.

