### Secondary outcome and other study measures

We will also evaluate several secondary outcomes. These will include an additional measure of receipt of test results based on medical records. Study participants will complete release forms (as applicable) in order to grant permission to study staff to review their medical records, including HIV and HCV testing records. Other secondary outcomes will include self-reported sexual risk behaviors and drug use practices such as (i) counts of unprotected vaginal and anal sex acts in the past 3 months with any sex partner, (ii) use of any drugs in the past 3 months, and (iii) unsafe injection practices. Additional measures will evaluate linkage to care by measuring the proportion of patients who initiated HIV care or HCV care before the 3-month follow-up among those whose test results were positive for HIV and/or HCV. Linkage to care for HIV or HCV will be measured separately, to account for variations in barriers to initiating care, which may be greater for HCV than barriers to initiating HIV medical care [67].

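### Linkage to care names different events in the outcome and data sections, and the listed questions do not cleanly give attended care for HIV and HCV separately

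*Protocol article*

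**What the plan says.** Four places in the protocol article bear on this outcome.

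- **Secondary outcome and other study measures.** Linkage is assessed through "measuring the proportion of patients who initiated HIV care or HCV care before the 3-month follow-up". The denominator is restricted to patients with a positive result: "among those whose test results were positive for HIV and/or HCV". The section adds that "Linkage to care for HIV or HCV will be measured separately", because barriers may be greater for HCV than for HIV.
- **Data sources, linkage to medical care.** The item is introduced differently: "We will also collect data on initiation of treatment among HIV and/or HCV positive patients, using the following questions". Questions 1 and 2 are worded "1) Did you have an appointment with a medical provider for HIV services? (2) Did you have an appointment with a medical provider for HCV". Item 3 asks for the number of medical appointments made, the number attended since the last interview, and whether ART or HCV treatment was started.
- **Study intervention.** Intervention patients with a reactive result "will be actively linked immediately to a healthcare provider for further evaluation and confirmatory testing". Controls are referred to a provider inside the treatment organization, or passively to other facilities.
- **Empirical analysis.** Linkage is a categorical variable analysed much like the primary outcome. No rule says which answer, or combination of answers, makes a patient linked.

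**The concern.** Having an appointment booked, attending a visit and starting drug treatment are different steps of the care cascade, and they yield different rates. The outcome section uses entry to care; the data section uses start of treatment in its lead-in and an appointment in its questions. A patient who attends HCV care but has not begun HCV treatment is linked under the first description and not under the second.

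The ambiguity matters more here because the arms differ by design at this very step. If an appointment that was only scheduled counts, staff who arrange it in the intervention arm help to produce the outcome, while controls rely mainly on referral. The comparison could then partly record that the intervention was carried out. An analysis plan can choose among the answers collected, but it cannot change what a question asked once the data are in.

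**Working it through.** **1. Is there a stated figure to reproduce?** Not for linkage: no rate and no expected number of positives is given. The only stated size belongs to the primary outcome, and it reproduces (pooled-variance two-proportion formula, two-sided 0.05, 80% power). CDOP at 50% v 80% needs 39 per arm, 78 in all, and 78/0.75 = 104. MTAA at 55% v 80% needs 54 per arm, 108 in all, and 108/0.80 = 135. The total is 104 + 135 = 239. This point does not touch that figure.

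**2. Which event can each item supply?**

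- Questions 1 and 2: by infection, but scheduled or attended is left open.
- Item 3, appointments made: scheduling only, not by infection.
- Item 3, appointments attended: attendance, not by infection and not limited to HIV or HCV visits.
- Item 3, start of ART or HCV treatment: by infection, but a later event than entering care.

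No single item is both specific to the infection and explicit about attendance, which is what the outcome section needs.

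**3. Do the items work in combination?** Only for some patients.

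- Attended = 0: not linked for either infection. Resolved.
- Attended = made: every appointment was kept, so a yes to question 1 or 2 means attended. Resolved.
- Attended above 0 but below made: not resolved. Take a co-infected patient who answers yes to both questions, with three appointments made and one attended. The visit kept may have been for HIV, for HCV, or for neither. A patient positive for HCV alone, with two made and one attended, has the same problem if one was an ordinary primary-care visit, and both programs are co-located with a primary care center.

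**4. Could the choice of item matter? Illustration on assumed rates only.** Suppose attendance is truly equal in the arms, but a share pI of intervention positives and pC of control positives report an appointment. With n positives per arm and p̄ = (pI + pC)/2, the chance of a significant difference is about

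Φ( [ |pI − pC| − 1.96·√(2p̄(1 − p̄)/n) ] / √([pI(1 − pI) + pC(1 − pC)]/n) ).

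For n = 10, pI = 0.95, pC = 0.50: p̄ = 0.725, and the two standard errors are √(2 × 0.725 × 0.275/10) = 0.1997 and √((0.0475 + 0.25)/10) = 0.1725. Then (0.45 − 1.96 × 0.1997)/0.1725 = 0.34, and Φ(0.34) = 0.63.

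| Positives per arm | 95% v 50% | 95% v 60% | 95% v 80% |
|---|---|---|---|
| 10 | 0.63 | 0.46 | 0.17 |
| 15 | 0.82 | 0.64 | 0.23 |
| 25 | 0.97 | 0.87 | 0.36 |

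The approximation is rough at these sizes. Exact calculation with Fisher's test gives 0.43, 0.74 and 0.95 for 95% v 50%, and 0.02, 0.08 and 0.20 for 95% v 80%. An attendance-based outcome would reject in about 5% of trials or fewer, because attendance is equal by assumption.

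**The case against.** The strongest reply has four parts.

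- **Data sources lists what is collected and does not score the outcome.** This is correct. A reader might infer that the protocol defines linkage as an appointment, or as treatment start. It does neither: the definition is initiation of care, and the deciding item is left open.
- **Attendance is collected.** Also correct: item 3 separates appointments made from appointments attended. What remains is that the count is not split by infection as worded, so step 3 leaves some patients unresolved. The article may paraphrase a fuller questionnaire that does split it, and that limits the weight.
- **Better linkage is what the intervention is for.** Correct again. Active linkage is a deliberate component, and a higher rate of attended care would be a genuine effect. A reader might infer that the outcome is met automatically in the intervention arm. The documents do not support this: Study intervention never calls the active link an appointment, and "1) Did you have an appointment with a medical provider for HIV services" can be read as a visit that took place. The bias arises only if scheduling alone is counted.
- **Any large false difference is built in by assumption.** This stands. The 45-point gap in the first column of the table requires many unattended appointments among intervention positives and none among controls. Controls are referred too, some within the same organization, so they may also hold appointments that they do not keep. The illustration also treats positives as one group, whereas HIV and HCV are to be measured apart. Enrollment is limited to people who report negative or unknown status, so new HIV positives may be very few, and the table cannot be carried over to HIV linkage.

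Item-level scoring may sit in a fuller protocol or analysis plan, and its absence from the article is no fault. The differing event names and the wording of the questions are on the page.

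**Conclusion.** The point holds as an inconsistent and partly unmeasurable definition. The outcome section names entry to care by infection; the data section names treatment start and asks about appointments; and the one item on attendance is not infection-specific. Because active linkage is given to one arm only, scoring scheduled appointments could introduce a between-arm measurement bias.

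Its size cannot be computed from the documents. On the assumed rates, the chance of a spurious significant result ranges from about 2% (10 positives per arm, 95% v 80%, Fisher's test) to about 97% (25 per arm, 95% v 50%, normal approximation). That range shows only that the choice of item could decide the result, not that it will. Linkage is a secondary measure, and neither the primary outcome nor the sample size is affected. The weight is minor to moderate.

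**What to change.** - Use one event in both sections: at least one attended medical visit for HIV (or HCV) care between randomization and the 3-month assessment, for each infection separately.
- Reword questions 1 and 2 to ask whether the patient attended, and split item 3 by infection.
- Report start of ART or HCV treatment as a separate outcome, and appointments made as a process measure.
- Add a sensitivity analysis that does not count the immediate hand-over or confirmatory-testing contact. Whether that contact is itself entry to care is debatable, so its exclusion should not be part of the main definition.

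**Cost.** Two questions reworded, one item split and one sentence in the outcome definition, with no added patients or visits. Trial status says recruitment had not begun, so the questionnaire can still be changed. The reported linkage rate may be lower than one based on appointments.

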### Power and sample size

We designed the trial to estimate the effects of on-site bundled rapid HIV/HCV testing on receipt of test results separately in each of the two types of SUD treatment facilities (MTAA and CDOP). Based on preliminary data from the study sites for the standard of care, we assumed that 50 % of control group participants enrolled at the CDOP facility will receive their HIV and HCV results after 1 month. We assumed that 55 % of control group participants receive their HIV and HCV test results after 1 month in the MTAA program, which treats a higher proportion of PWIDs. Based on findings from the evidence-based rapid HIV intervention that informs this study [25], we assumed that 80 % of patients in the intervention group would receive their HIV and HCV test results within 1 month of randomization. To detect such intervention effects on the basis of a two-sample, chi-squared test for independent proportions with 80 % power and α = 0.05, we will require 78 patients in CDOP and 108 patients in MTAA facilities. We assumed an 80 % follow-up rate among participants enrolled at the MTAA program. We assumed a slightly lower follow-up rate among participants enrolled at the CDOP facility (75 %) because adherence to behavioral SUD treatment is lower among CDOP patients at Promesa Inc. These are conservative assumptions. For example, during the trial of the rapid HIV testing EBI, which informs this study, researchers achieved a 98 % 1-month follow-up rate [25]. In total, we obtained a total sample size of 239 participants (104 in CDOP and 135 in MTAA).

### Empirical analysis

The primary outcome is a categorical variable denoting self-reported receipt of rapid HIV and rapid HCV test results at 1-month post-randomization. We will use a generalized estimating equation model, which includes covariates for type of drug use (injection/non-injection) and location of primary care provider (study site versus elsewhere). The model will also include indicator variables for HIV/HCV testing intervention status and the type of SUD treatment facility (MTAA versus CDOP), where the participants were recruited. The primary test of our study hypothesis will be a two-degree of freedom test of significance of the intervention across the two types of SUD treatment facilities. In post-hoc tests, the efficacy and effect size in each type of SUD treatment facility will be examined. To do so, we will include an interaction between variables identifying study groups (intervention versus control) and type of SUD treatment facility (MTAA versus CDOP). The primary analysis will be intent-to-treat, where everyone is included in the study group to which they were randomized, regardless of receipt of intervention. In sensitivity analyses, participants who have died or who have been lost to follow-up will be counted as not having tested. We will adjust for baseline covariates that may be associated with attrition from the study sample using inverse probability reweighting procedures as recommended for the GEE model [69].

The secondary outcomes related to linkage to HIV and HCV care, as well as to drug use, are categorical variables. They will be analyzed using techniques similar to those used for the primary outcome. This is also the case for indicators related to HIV and HCV prevalence among patients tested by bundled rapid testing versus standard of care. The number of unprotected sex acts over a period of time is a count variable and will be modeled using Poisson or negative binomial regression (if the variable is over-dispersed) or the zero-inflated version of these if necessary. Type of drug use (injection/non-injection) and the recruitment site (MTAA or CDOP) will be included as covariates. If other covariates predict missing data, they will also be included as control variables. All analyses of secondary outcomes will focus on the pooled data, that is, CDOP + MTAA programs. Because of the limited sample size, we will not conduct formal mediation analyses.

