### Study assessments

There will be three assessments during this trial of on-site bundled rapid HIV/HCV testing. These will include a baseline assessment administered prior to randomization, a follow-up assessment conducted 1 month after randomization, and a final assessment conducted 3 months after randomization (see Fig. 1).

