### Primary outcome

The primary outcome will be self-reported receipt of HIV and HCV test results. The primary outcome will be assessed one-month post-randomization. Our use of self-reported receipt of test results is consistent with the use of self-reports as the primary outcome for evaluating rapid HIV testing interventions [25].

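### The analysis section words the primary outcome as receipt of rapid test results, contradicting the outcome definition and the 50% and 55% control rates; most likely a drafting error, but it changes who counts as a success

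*Protocol article*

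**What the plan says.** The protocol article describes the primary outcome in two ways.

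- Primary outcome section: "The primary outcome will be self-reported receipt of HIV and HCV test results". On timing: "The primary outcome will be assessed one-month post-randomization". No test type is named.
- Empirical analysis section: "The primary outcome is a categorical variable denoting self-reported receipt of rapid HIV and rapid HCV test results at 1-month post-randomization". Here the test type is attached to each of the two infections.

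Three other sections bear on which wording can be meant.

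- Study intervention, on the control arm: "The SOC is venipuncture whole blood laboratory-based HIV and HCV testing with delayed results (enzyme immunoassay"). Once follow-up is over, "all patients in the control group will be offered access to the on-site bundled rapid HIV/HCV testing intervention".
- Study assessments, on when follow-up ends: "a final assessment conducted 3 months after randomization".
- Power and sample size, on the control arm: "we assumed that 50 % of control group participants enrolled at the CDOP facility will receive their HIV and HCV results after 1 month", and "We assumed that 55 % of control group participants receive their HIV and HCV test results after 1 month in the MTAA program". The section bases these rates on preliminary site data for the standard of care.

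**The concern.** The two wordings define different endpoints, and the difference falls on one arm. Take a control participant who had blood drawn at the health center and learned both laboratory results two weeks later. Under the Primary outcome section this person is a success. Under the literal Empirical analysis wording the same person is a failure, because neither result came from a rapid test. Intervention participants are hardly touched, since rapid tests are what that arm is offered.

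The trial asks whether bundled rapid testing increases receipt of HIV and HCV results. An endpoint that only rapid results can satisfy would mostly record who was given access to rapid tests, which randomization itself decides. Neither the intention-to-treat rule nor the choice of model would correct that, because the problem lies in how the variable is defined.

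**Working it through.** **Inputs.** From Power and sample size: control rates 0.50 (CDOP) and 0.55 (MTAA); intervention rate 0.80; chi-squared test of two proportions, 80% power, α = 0.05; follow-up 75% (CDOP) and 80% (MTAA); stated results 78 and 108 evaluable, 104 + 135 = 239 enrolled. Assumed, because not stated: 1:1 allocation and a two-sided test.

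**Step 1: reproduce the plan's figures.** With p̄ the mean of the two rates, the number per arm is

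n = [1.960·√(2p̄(1−p̄)) + 0.842·√(p₁(1−p₁) + p₂(1−p₂))]² / (p₂−p₁)²

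- CDOP: p̄ = 0.65; n = [1.960·√0.455 + 0.842·√0.41]² / 0.30² ≈ 38.5, so 39 per arm and 78 in all. 78/0.75 = 104. Power with 39 per arm is 80.5%.
- MTAA: p̄ = 0.675; n = [1.960·√0.43875 + 0.842·√0.4075]² / 0.25² ≈ 53.9, so 54 per arm and 108 in all. 108/0.80 = 135. Power with 54 per arm is 80.1%.
- Total: 104 + 135 = 239.

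All stated figures are reproduced. Other common variants do not give them: with continuity correction 90 and 124, with unpooled variance 72 and 104, one-sided 62 and 86.

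**Step 2: which definition do these figures use?** The 50% and 55% describe controls under standard of care, which is laboratory immunoassay. They can be success rates only if laboratory results count. The sample size is therefore built on the test-neutral outcome.

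**Step 3: apply the literal analysis wording.** The trial supplies no rapid test to controls before the end of follow-up at 3 months, and the outcome is measured at 1 month. The documents give no rate of rapid testing obtained elsewhere, so I take a control rate of 0% to 5% as an assumption and keep 80% in the intervention arm.

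| Control rate | Difference | Evaluable patients needed per site |
|---|---|---|
| 50% (CDOP, as planned) | 30 points | 78 |
| 55% (MTAA, as planned) | 25 points | 108 |
| 5% (literal wording) | 75 points | 12 |
| 2% (literal wording) | 78 points | 10 |
| 0% (literal wording) | 80 points | 10 |

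At the planned evaluable numbers, power under the literal wording is essentially 100%.

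**Step 4: participants affected.** On the plan's assumptions, 39 × 0.50 + 54 × 0.55 = 19.5 + 29.7 ≈ 49 of the 93 evaluable controls would be successes under the Primary outcome section. If all of their results came from the laboratory, all 49 would be failures under the literal analysis wording.

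**The case against.** The strongest reply is that the rest of the article settles the meaning. The Abstract, Study design and Conceptual/theoretical framework sections all describe the trial outcome as receipt of HIV and HCV results without a test type, as does the Primary outcome section. The control rates in Power and sample size need laboratory results to count. The Empirical analysis section itself does not keep to the narrow reading: its sensitivity analysis scores losses as not tested, rather than as lacking a rapid test, and its next paragraph refers to patients tested under standard of care. This is also a journal article, and the full protocol or analysis plan may word the variable correctly.

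Most of that stands. It shows that the extra word is very probably a slip. It does not remove the contradiction: the sentence is a positive definition of the primary analysis variable, not a detail left to another document.

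Several stronger readings are tempting and are not supported.

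- A reader might infer that the trial will be positive by construction with an 80-point difference. That follows only if the literal word is applied against the outcome and sample-size sections.
- A reader might infer that the sample size is wrong. It is not.
- A reader might infer that controls never receive rapid tests, so that their rate is zero by definition. They are offered rapid testing after follow-up, and nothing shown rules out a rapid test elsewhere. Near 0% at 1 month is an expectation.
- A reader might infer that the Primary outcome section says any method counts. It is silent on method; neutrality is inferred from the control rates.
- A reader might infer that the questionnaire asks about rapid tests only. Its items on receipt of results are not reproduced, so there is no evidence either way.

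**Conclusion.** The concern holds as an internal contradiction in the definition of the primary outcome. Taken literally, the Empirical analysis wording would move the expected control rate from 50% and 55% to near 0%, and the differences from 30 and 25 points to about 80 (75 if 5% of controls found a rapid test elsewhere). The endpoint would then reflect assignment rather than improved receipt of results. This size is conditional on the literal reading and on the plan's 80% intervention rate; it is not a forecast of bias in the trial as intended. The intended definition can be recovered from the other sections, and every sample-size figure agrees with it. The wording should still be corrected, because it concerns the primary endpoint and changes who counts as a success in one arm.

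**What to change.** In Empirical analysis, delete *rapid* in both places where it qualifies the test results. State that the primary outcome is self-reported receipt of both HIV and HCV test results by the 1-month assessment, with rapid and laboratory results counted alike in both arms. This brings the sentence into line with the Primary outcome section and with the control rates in Power and sample size. If the full protocol or analysis plan carries the same sentence, correct it there too.

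The cost is one sentence of wording. The sample size, visits and model stay as they are. The Trial status section says recruitment had not begun when the article was written.

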### Eligibility and recruitment

Participants must be (1) able and willing to provide informed consent, (2) seeking or currently receiving SUD treatment services (excluding alcohol only) at the participating treatment programs, (3) at least 18 years old, (4) able to communicate in English, (5) willing to sign a release form that will allow medical record review (to corroborate self-reports of receipt of test results), (6) willing to provide locator information, (7) self report being HIV and HCV negative, or report not knowing their HIV and HCV status, and (8) not have received results of an HIV or HCV test initiated within the last 12 months. We will employ several recruitment strategies to facilitate enrollment to reach our target sample size, including trained research staff, posters, and collaborating with staff of the study site to identify interested patients. We will promote participant retention by collecting locator information, which will be used to contact participants to remind them of follow-up visits and to locate participants who cannot be reached. Participation in the study is voluntary, and participants may choose to end their involvement at any time.

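### The adjusted GEE prescribed for HIV linkage will very probably be inestimable; for HIV prevalence it breaks down usually only if undiagnosed HIV is rarer than about 1.6%

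*Protocol article*

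**What the plan says.** The Empirical analysis section describes the primary model: "We will use a generalized estimating equation model, which includes covariates for type of drug use (injection/non-injection) and location of primary care provider". Indicators for study arm and treatment facility are added. With the intercept that makes five parameters, or six when the arm-by-facility interaction is fitted.

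Of the categorical secondary outcomes, which include linkage to HIV care, the same section says: "They will be analyzed using techniques similar to those used for the primary outcome". The next sentence adds: "This is also the case for indicators related to HIV and HCV prevalence among patients tested by bundled rapid testing versus standard of care".

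The secondary outcome section restricts linkage to participants "among those whose test results were positive for HIV and/or HCV" and states: "Linkage to care for HIV or HCV will be measured separately". The eligibility section admits people who "self report being HIV and HCV negative, or report not knowing their HIV and HCV status", and who must "not have received results of an HIV or HCV test initiated within the last 12 months".

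For the count outcome, the Empirical analysis section names alternatives in case of over-dispersion or excess zeros. It names none for a sparse binary outcome. Limited sample size is mentioned only as the reason for omitting mediation analyses.

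**The concern.** HIV linkage is a named secondary outcome, and its denominator is only those trial participants found to be HIV-positive. Eligibility removes people who report being positive and people who recently received results, so essentially only undiagnosed HIV can contribute. A five-parameter model needs more data than such a group is likely to supply.

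Two kinds of failure are possible. The model may not be fittable at all, because there are too few positives or a covariate does not vary among them. Or it may be separated, so that a log odds ratio runs off towards infinity. In a GEE the second failure can go unflagged, because the sandwich standard error may stay small while the coefficient diverges. HIV prevalence has a larger denominator but the same weakness whenever one arm has no positives.

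The stake is that a secondary result is either unavailable under the stated method or, depending on the test chosen, misleading.

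**Working it through.** **1. The plan's own figure.** The sample size section gives 80% receipt against 50% (CDOP) and 55% (MTAA), α = 0.05, 80% power, and follow-up of 75% and 80%. Per arm, n = [1.960·√(2p̄(1−p̄)) + 0.8416·√(p₁(1−p₁)+p₀(1−p₀))]² / (p₁−p₀)².
- CDOP: (1.960×0.6745 + 0.8416×0.6403)² / 0.09 = 38.5, so 39 per arm, 78 in all; 78/0.75 = 104.
- MTAA: (1.960×0.6624 + 0.8416×0.6384)² / 0.0625 = 53.9, so 54 per arm, 108 in all; 108/0.80 = 135.
- Total 239. This reproduces exactly and is not in dispute.

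**2. Participants expected to have results** (1:1 allocation, the plan's receipt rates).
- Intervention: 119.5 × 0.80 = 95.6.
- Control: 67.5 × 0.55 + 52 × 0.50 = 63.1.
- Total about 159.

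**3. HIV-positives.** The protocol gives no prevalence of undiagnosed HIV in eligible patients. I assume 0.5% to 5% and show 10% as an extreme. Expected count = 159 × prevalence.

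**4. HIV prevalence outcome.** With the same true prevalence π in both arms, P(no positives in at least one arm) = 1 − [1 − (1−π)^96]·[1 − (1−π)^63].

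**5. HIV linkage outcome.** I simulated 2,000 trials per scenario with a logistic independence GEE on arm, facility, drug-use type and primary care location. Assumptions not in the documents: 70% linked in both arms, 35% injecting, 60% with primary care at the study site. A trial counts as failed if the model cannot be fitted or is separated. The easier arm-only model is shown as well, as is the favourable case of all 239 being tested.

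| Assumed HIV prevalence | 0.5% | 1% | 2% | 3% | 5% | 10% |
|---|---|---|---|---|---|---|
| Expected HIV-positives among 159 | 0.8 | 1.6 | 3.2 | 4.8 | 8.0 | 15.9 |
| Prevalence: no positives in an arm | 90% | 71% | 38% | 19% | 5% | 0.1% |
| Linkage, adjusted model fails | >99% | >99% | >99% | >99% | 95% | 57% |
| Linkage, arm-only model has a zero cell | >99% | 99% | 94% | 84% | 60% | 20% |
| Linkage, adjusted model fails, all 239 tested | >99% | >99% | >99% | 97% | 77% | 23% |

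For HIV prevalence, the 50% point lies at π ≈ 1.6%. It moves to about 1.0% if all 239 are tested, and to about 2.0% if only the roughly 123 expected both to have results and to be followed up are counted.

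**6. What an empty cell does to the test** (arm-only GEE, participant as cluster).
- 2/96 v 0/63: coefficient 21.7, robust SE 0.71, fit reported as converged, robust Wald p ≈ 1e-202. Fisher's exact p = 0.52. On the same data the Wald test with model-based SE gives p = 0.9996 and a robust score test about 0.16.
- 1/96 v 0/63: robust Wald p ≈ 1e-97; Fisher p = 1.0.

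With no true arm effect on HIV prevalence, the robust Wald test in the adjusted model has p < 0.05 in 45%, 50%, 35%, 19% and 6% of trials at 0.5%, 1%, 2%, 3% and 5%. A robust score test under near-identical counts (95 v 63) gives 0.1%, 1%, 4.6%, 5.5% and 5.4%.

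**The case against.** The strongest reply is that the protocol names no robust Wald test. It fixes neither the standard error, nor the working correlation, nor the test statistic. A reader might infer from the figures above that the trial, followed as written, would often declare a false HIV difference. The documents do not support that: the inflation belongs to one customary test and disappears with a score or model-based test. An odds ratio of exp(21.7), in the billions, should also alert anyone who sees 2 events against 0. For the adjusted linkage model at low prevalence the usual failure is a model that cannot be fitted, which is plain to see. All of this stands, and the false-positive risk is therefore conditional.

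Second, a reader might infer that the trial can yield only a handful of HIV-positives. No passage says so. Eligibility makes small numbers plausible, but the count rests on an assumed prevalence, and at 10% it would be about 16. For HIV prevalence, breakdown is not the usual outcome above about 1.6%, and by 5% the arm effect is mostly estimable, though imprecise.

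Third, the wording is techniques that are similar, not identical. An analysis plan not shown could add a fallback, and a condensed article need not list one. The latitude is real. But the text does more than stay silent: it assigns a method to these outcomes, and that method is ill suited to HIV linkage over the whole 0.5% to 5% range.

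Fourth, the secondary outcome section says that linkage is measured separately for each infection, not that it is analysed separately, and HIV prevalence is called an indicator with no hypothesis attached. Separate models are the natural reading of separate measures, but this limits how much weight the prevalence part can bear.

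Finally, the quoted rule also covers HCV linkage, HCV prevalence and drug use. No failure has been shown for any of these.

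**Conclusion.** The point holds, chiefly for HIV linkage. With undiagnosed HIV at 0.5% to 5% and the plan's own receipt rates, the adjusted linkage model is inestimable or separated in roughly 95% or more of trials, and in 57% even at 10%. Dropping the covariates does not rescue it: a zero cell remains in 60% or more of trials up to 5%. These figures rest on the assumed prevalence, linkage rate and covariate mix. If all 239 were tested, failure would still be 97% at 3% and 77% at 5%.

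For HIV prevalence the point is narrower. An arm without positives is the usual result only below about 1.6%. Where it occurs, a spurious p-value is a risk if a robust Wald test is used, and not otherwise.

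Only secondary outcomes are affected. The primary analysis and the 239 are untouched. A change is worth making because the stated method has little chance of working for HIV linkage and a suitable one is cheap.

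**What to change.** In the Empirical analysis section, remove HIV linkage and HIV prevalence from the rule that sends them to the primary outcome's technique. State instead that each will be reported as counts by arm with exact confidence intervals. If a comparison is wanted, specify Fisher's exact test or Firth-penalised logistic regression with the arm term only and profile-likelihood intervals.

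The cost is one or two sentences, plus the loss of covariate adjustment for these two outcomes, which the expected counts could not support anyway. The rule can stay as it is for HCV linkage, HCV prevalence and drug use.
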